### **9.2.2.Secondary endpoints**

- Best overall response is defined as the best response across all time points (RECIST v1.1). Following RECIST v1.1 recommendations:
  - The best overall response is determined once all the data for the patient is known.
  - The best overall response will be classified as confirmed complete response (CR), unconfirmed complete response (CRu), confirmed partial response (PR), unconfirmed partial response (PRu), stable disease or progressive disease, as per RECIST v1.1 criteria.
  - As per RECIST v1.1 criteria, to be considered as “confirmed”, complete and partial responses will have to be confirmed at least 4 weeks later to ensure responses identified are not the result of measurement errors.
- Objective response rate at 6 months (6-month ORR) is defined as the proportion of patients with objective response (confirmed or unconfirmed) at 6 months.
- Progression-free status is defined as complete response (confirmed or unconfirmed), partial response (confirmed or unconfirmed) or stable disease more than 24 weeks as defined as per RECIST v1.1 criteria (appendix 3). 6-month progression-free rate (6-month PFR) is defined as the proportion of patients with progression-free status at 6 months. 4-month progression-free rate (4-month PFR) is defined as the proportion of patients with progression-free status at 4 months.
- Growth modulation index (GMI): GMI is defined for each patient as the ratio of its PFS on Regorafenib + Avelumab treatment to its PFS on the previous line of therapy. This method accounts for inter-patient variability, the patient serving as his/her own control and implies by the natural history of the disease that the PFS tends to become shorter in successive lines of therapy. It is thought that an anti-cancer agent should be considered effective if the GMI is greater than 1.3
- Progression-free survival (PFS) is defined as the time from study treatment initiation to the first occurrence of disease progression or death (of any cause), whichever occurs first. 1-year PFS rate and median PFS will be reported.

- Overall Survival (OS) is defined as the time from study treatment initiation to death (of any cause). 1-year OS rate and median OS will be reported.
- Safety profile of the association Regorafenib + Avelumab: Toxicity will be graded using the common toxicity criteria from the NCI v5.0.
- Pharmacodynamic activity:
  - archived tumor tissue will be collected for assessment of the tumor microenvironment.
  - to perform integrative assessment of biomarkers of efficacy (genetic, metabolomics profiling in blood/tissue at baseline and different study time points) and its prognostic value on efficacy.
- For the cohort B: To evaluate the antitumor activity based on Choi criteria in terms of 6-month PFR.

## 10. STATISTICAL CONSIDERATIONS

### 10.1. HYPOTHESES AND NUMBER OF SUBJECTS NEEDED

#### 10.1.1. Phase I trial

- The dose escalation part is designed to detect the MTD of Regorafenib given in association with Avelumab.
- The dose escalation design to identify the maximum tolerated dose will be the traditional 3+3 design. Adaptive designs, such a continual reassessment method (CRM) using likelihood inference do not appear relevant in this context given there are only three dose levels investigated and the toxicity profile of Regorafenib.
- A minimum of 3 patients and a maximum of 6 patients per dose level
- Since there are three dose levels investigated, a maximum of 12 eligible patients assessable for DLT is expected.

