| Number of patients                      | Phase I (escalation part): 6-12 patients
Phase II (expansion cohorts): 735 patients                                                                                                                                                                                                                                                                                                                                                                                                                                                                                                                                                                                                                                                                                                                                                                                                                                                                                                                                                                                                                                                                                                                                                                                                                                                                                                                                                                                                                                                                                                                                                                                          |

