#### **PHASE 1: DOSE ESCALATION**

- 3 dose levels of Regorafenib will be investigated in combination with Avelumab:

| Level       | -1      | 1       | 2       |
|-------------|---------|---------|---------|
| Avelumab    | 10mg/kg | 10mg/kg | 10mg/kg |
| Regorafenib | 80 mg   | 120 mg  | 160 mg  |

- The starting dose of Regorafenib is 120 mg (dose level 1).
- The maximum dose of Regorafenib administered (160 mg) will not be exceeded.
- No skipping of the dose will be allowed.
- For a given patient, dose will never be escalated.
- Patients will be allocated to the 3 dose levels following a 3 + 3 design.
- A minimum of 3 patients and a maximum of 6 patients will be entered on each dose level.
- All 3 patients within a dose level will be observed during 28 days (the period of observation of DLTs) before accrual to the next higher dose level may begin.
- Dose escalation will proceed according to the following scheme:

| Number of patients with DLT at one dose level | Escalation Decision Rule                                                                                                                                                                                                                                                                                                                                                                                                         |
|-----------------------------------------------|----------------------------------------------------------------------------------------------------------------------------------------------------------------------------------------------------------------------------------------------------------------------------------------------------------------------------------------------------------------------------------------------------------------------------------|
| 0 out of 3                                    | Enter 3 patients at the next dose level.                                                                                                                                                                                                                                                                                                                                                                                         |

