### 3.2.3. Dose levels

Dose escalation study assessing 3 doses level of Regorafenib given in combination with Avelumab (fixed dose).

| Dose level   | Regorafenib       |
|--------------|-------------------|
| -1           | 80 mg once daily  |
| 1 (starting) | 120 mg once daily |

|   |                   |
|---|-------------------|
| 2 | 160 mg once daily |
|---|-------------------|

- The starting dose of Regorafenib is 120 mg once daily.
- The maximum dose of Regorafenib administered (160 mg once daily) will not be exceeded.
- No skipping of the dose will be allowed.
- For a given patient, dose will never be escalated.
- Patients will be allocated to 2 doses levels following a 3 + 3 design.
- A minimum of 3 patients and a maximum of 6 patients will be entered on each dose level.
- All 3 patients within a dose level will be observed during 28 days (the period of observation of DLTs) before accrual to the next higher dose level may begin.
- Dose escalation will proceed according to the following scheme:

| Number of patients with DLT at one dose level | Escalation Decision Rule                                                                                                                                                                                                                                                                                                                                                                                                            |
|-----------------------------------------------|-------------------------------------------------------------------------------------------------------------------------------------------------------------------------------------------------------------------------------------------------------------------------------------------------------------------------------------------------------------------------------------------------------------------------------------|
| 0 out of 3                                    | Enter 3 patients at the next dose level.                                                                                                                                                                                                                                                                                                                                                                                            |

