| $\geq 2$                                      | Dose escalation will be stopped. This dose level will be declared as the maximum administered dose (MAD). Three additional patients will be entered at the next lowest dose level if only 3 patients were treated previously at that dose.                                                                                                                                                                                          |
| 1 out of 3                                    | Enter at least 3 more patients at this dose level. 
 
• If 0 of these 3 patients experience DLT, proceed to the next dose level.
 
• If 1 or more of this group suffer DLT, dose escalation will be stopped, and this dose is declared as the MAD. Three additional patients will be entered at the next lowest dose if only 3 patients were treated previously at that dose.
 
 |
| $\leq 1$ out of 6                             | If this is the highest dose level, this will be the maximum tolerated dose (MTD).
Else, proceed to the next dose level.                                                                                                                                                                                                                                                                                                          |

- As described above, the maximum administered dose (MAD) for Regorafenib is the dose in which  $\geq 2/3$  or  $\geq 2/6$  patients experience DLT.
- If the MAD for Regorafenib is seen at the starting dose level, then dose level “-1” will be the recommended dose. (Note: upon dose reduction, MAD criteria could be fulfilled but no tolerable combination may be found to continue into Phase II).
- The MTD for Regorafenib is defined as the highest dose at which no more than 1 in 6 of the patients in the cohort experienced a DLT during the period of observation of DLTs.
- The steering committee will meet before proceeding or not to each dose escalation. In addition, in case of discussion regarding the DLT status of a specific patient, the steering committee will be consulted to resolve any specific question regarding the DLT status (see section 12.1).
- The sponsor may decide to submit the cConclusions of the steering committee for the definition of MTD and the RP2D to an independent data monitoring committee (IDMC) before opening the phase II trials.

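### The phase I maximum of 12 assessable patients does not follow from three dose levels of up to 6 each; if level -1 is tested, the 3+3 rules allow up to 18

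*Protocol*

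**What the plan says.** Section 10.1.1 sets "A minimum of 3 patients and a maximum of 6 patients per dose level". It then names the count of three levels as the reason why "a maximum of 12 eligible patients assessable for DLT is expected". The statistical considerations in the synopsis repeat both statements, and the synopsis entry for the number of patients reads "Phase I (escalation part): 6-12 patients".

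The design text is in section 3.2.3 and, nearly identically, in the synopsis:

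- **Levels.** There are three: -1 (80 mg), 1 (120 mg) and 2 (160 mg). "The starting dose of Regorafenib is 120 mg once daily", so escalation starts at the middle level.
- **Patients per level.** "A minimum of 3 patients and a maximum of 6 patients will be entered on each dose level".
- **Allocation.** The synopsis says: "Patients will be allocated to the 3 dose levels following a 3 + 3 design". The matching bullet in section 3.2.3 says two levels instead of three, directly under its own three-level table.
- **Back-fill once a level is the maximum administered dose (MAD).** The rule reads: "Three additional patients will be entered at the next lowest dose level if only 3 patients were treated previously at that dose".
- **MAD at the starting level.** Level -1 becomes the recommended dose. A bracketed note adds that the MAD criteria might also be met after the reduction, so that no tolerable combination is found.

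**The concern.** The sentence in section 10.1.1 presents 12 as a consequence of three levels, but with up to 6 patients per level three levels give 18. The figure and its reason do not belong together, and the protocol gives two different counts of the levels used. A reader cannot tell whether 12 is a true maximum for a two-level escalation or a miscount for a three-level one. At stake is whether the reported phase I size can be traced to the design. Phase I analyses are descriptive, and no phase II decision rule uses this number.

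**Working it through.** **Inputs (sections 3.2.3 and 10.1.1, synopsis).** Levels -1, 1 and 2, starting at level 1; 3 to 6 patients per level; 0/3 escalates; 1/3 adds 3 more; 2 or more DLTs make the level the MAD; the level below is then filled to 6 if only 3 were treated there.

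**The plan's figure.** 2 levels × 6 = 12 reproduces it. 3 levels × 6 = 18 does not.

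**Is 18 reachable?** If level -1 is treated, yes:

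1. Level 1: 0/3, so escalate (3 patients).
2. Level 2: 1/3, three more, at least one further DLT, so MAD (6 patients).
3. Level 1: three more; 2 or more DLTs among the 6, so level 1 meets the MAD definition (6 patients at this level).
4. Level -1: 1/3, three more (6 patients).

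Total 6 + 6 + 6 = 18. If level -1 is never treated, the maximum is 12. However, 2 or more DLTs in the first three patients would then end phase I at 3 patients, below the synopsis minimum of 6.

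**How likely is more than 12?** Every such path starts with 0/3 at level 1, has level 2 declared the MAD, and has level 1 fail when it is filled to 6. (If level 1 passes at 1/6 it already has 6 patients and is not reopened. If it fails at once, the total is at most 6 + 6 = 12.) Let p be the DLT rate at a level and q = 1 - p:

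- A = q₁³: 0/3 at level 1
- B = 3p₁²q₁ + p₁³: 2 or more DLTs in the three added patients
- m₃ = 3p₂²q₂ + p₂³: level 2 is the MAD after 3 patients
- m₆ = 3p₂q₂²(1 - q₂³): level 2 is the MAD after 6 patients
- u = 3p₋₁q₋₁²: level -1 goes to 6 patients

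With 3 at level 2, the total passes 12 only if level -1 goes to 6. With 6 at level 2, it passes 12 in any case. So P(N > 12) = A·B·(m₆ + m₃·u) and P(N = 18) = A·B·m₆·u.

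For assumed rates 8/15/30%: A = 0.6141, B = 0.0608, m₆ = 0.2897, m₃ = 0.216, u = 0.2031. P(N > 12) = 0.6141 × 0.0608 × (0.2897 + 0.216 × 0.2031) = 0.012.

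The rules do not say what follows 0/3 at a level with no next step. If it is expanded to 6 at levels 2 and -1, m₆ gains q₂³·m₃ and u gains q₋₁³. For the same rates, m₆ = 0.3638 and u = 0.9818, so P(N > 12) = 0.6141 × 0.0608 × (0.3638 + 0.216 × 0.9818) = 0.021.

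| Assumed DLT rates, levels -1/1/2 | P(N > 12), 0/3 not expanded | P(N > 12), 0/3 expanded | P(N = 18), not expanded / expanded |
|---|---|---|---|
| 8/15/30% | 1.2% | 2.1% | 0.2% / 1.3% |
| 12/25/40% | 2.9% | 5.0% | 0.6% / 2.6% |
| 20/30/50% | 3.9% | 6.2% | 0.9% / 2.6% |

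The protocol gives no DLT rates; these are assumptions. The maximum of 18 does not depend on them.

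**The case against.** The strongest reply is that the route to 18 is inferred. The back-fill sentence covers only a level where 3 patients were already treated, so it does not open level -1. The rule for a MAD at the starting level names level -1 as the recommended dose and prescribes no cohort there. With the two-level wording of section 3.2.3, 12 is then exactly right. This stands in part: a reader might infer that the protocol plainly prescribes 18, and it does not. But the other reading is no cleaner. The note after dose reduction presupposes DLT data at level -1, the minimum of 3 patients applies to each level, the synopsis allocates patients to three levels, and section 10.1.1 itself rests the figure on three levels.

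A second reply is that 12 is only an expected figure. Under the assumed rates it does cover about 94-99% of outcomes. But the sentence calls it a maximum, and the synopsis gives a closed range.

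A third reply stands: the matter is settled in practice. Section 7.3 gives 160 mg as the phase II dose defined in phase I. Any total above 12 requires level 2 to have been declared the MAD, which does not fit with 160 mg carried forward. Replacement of patients does not explain the gap, because the figure counts assessable patients only.

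**Conclusion.** The point holds as an inconsistency in a stated planning figure. Twelve does not follow from three levels of up to 6; it follows from two. If level -1 is tested, the maximum is 18, but exceeding 12 is unlikely: about 1-4%, or 2-6% with expansion of 0/3, over the assumed DLT rates.

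A reader might go further and infer that the trial ran over its declared size, or that its authorisation rested on a wrong number. The documents do not support this. No phase I counts are reported, and the dose in section 7.3 implies that the completed phase I stayed within 12. Remaining conduct and phase II inference are unaffected, so the importance is minor.

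**What to change.** Reconcile five places: the synopsis entries for number of patients, phase 1 dose escalation and statistical considerations, and sections 3.2.3 and 10.1.1. Two forms would be consistent:

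- a design maximum of 18 DLT-assessable patients, with 12 as the usual upper range when only two levels are used; or
- a statement that only two levels are counted towards the maximum, with the reason.

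In either case, section 3.2.3 and the synopsis should give the same number of levels, and the text should say whether patients are treated at level -1 after a MAD at the starting level. Which rule applies is for the sponsor to state; this review does not propose one. The cost is a text correction in the five places, with no change to conduct or analysis.

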#### 10.1.2. Phase II trials: Cohorts A, B, C, D, E, F, G

Independently for each of these phase II trials, a Bayesian approach will be used following an adaptive trial design, allowing for smaller and more informative trials, specifically tied to decision making within a drug development program. This process allows updating knowledge gradually rather than restricting revisions in a trial design with fixed sample sizes.

In each phase II trial:

- A maximum sample size of 50 patients will be included.
- The analysis of the primary endpoint (ORR under treatment for cohorts A as well as C to G; 6-month PFR for cohort B) will be carried out sequentially, with interim analyses planned after 16-week follow-up of the first 10 patients and then every 5 patients. Inclusions will not be suspended between interim analyses, except in case of an important accrual rate in a given given trial (2 patients/center/months during at least 3 months).
- ORR (for cohorts A as well as C to G) or 6-month PFR (for cohort B) will be estimated in the eligible population assessable for efficacy (section 10.2.2). The probability of success (ORR under treatment or 6-month PFR) will be estimated from a beta-binomial model (Zohar et al., 2008). Initial parameters of the model will be pre-specified (the prior distribution represents the knowledge of the non-progression probability prior to observing the data). Successive results observed will then be used to update and refine the distribution, generating the so-called posterior distribution.
- In the absence of a strong idea about the response rates to be observed, a non-informative prior distribution (beta (1,1)) will be considered.
- Maximal response probability thresholds (based on the investigator' opinions) and minimal response probability threshold have been defined as follows:
  - Cohort A/E:  $p_0=5\%$  versus  $p_1=20\%$
  - Cohorts B/C/D/F:  $p_0=20\%$  versus  $p_1=40\%$
  - Cohorts G:  $p_0=10\%$  versus  $p_1=25\%$
- At each update of the distribution (interim analysis), a stopping rule for inefficacy will recommend stopping the trial if there is a high predictive probability ( $\geq 80\%$ ) that the ORR (for cohorts A as well as C to G) or 6-month PFR (for cohort B) is lower or equal to the minimal response probability threshold  $p_0$  defined for the cohort (Strata A and E:  $p_0=5\%$ ; Strata B/C/D/F:  $p_0=20\%$ ; Stratum G:  $p_0=10\%$ ).
- At each update of the distribution (interim analysis), a stopping rule for efficacy will recommend stopping the trial if there is a high predictive probability ( $\geq 80\%$ ) that the ORR (for cohorts A as well

as C to G) or 6-month PFR (for cohort B) is higher or equal to the the maximal response probability threshold  $p_1$  (Strata A and E:  $p_1=20\%$ ; Strata B/C/D/F:  $p_1=40\%$ ; Stratum G:  $p_1=25\%$ ).

- The trial will continue until the stopping rule applied at each interim analysis is met, or until the maximum sample size of 50 patients is reached.
- When a trial is not completed to allow efficacy analysis, descriptive data only are presented.

#### **10.1.3. Phase II trial: Cohort H (NSCLC)**

- We rely on a single-arm phase 2 trial based on an optimal two-stage Simon's design [91].
- Treatment will be considered promising if 6-month PFR ( $\geq 20\%$ ).
- Hypotheses are the following [62] :
  - 20% 6-month PFR (null hypothesis),
  - 40% acceptable 6-month PFR (alternative hypothesis),
  - 5% 1-sided type I error rate,
  - 80% power,
- A total of 43 eligible and assessable subjects will be necessary, with 13 assessable subjects recruited to the first stage.
- Stage 1: Following the inclusion of the first 13 assessable patients, if 3 or less patients are progression-free at 6 months (complete response, partial response or stable disease), the study will be terminated early. Otherwise, if 4 or more patients are progression-free at 6 months, the second group of subjects will be recruited.
- Stage 2: If at the end of recruitment, 13 patients or more are progression-free at 6 months (out of the 43 eligible and evaluable patients), treatment will be considered worthy of further testing in this disease (efficacy rate  $\geq 20\%$ ).
- Inclusions will not be suspended after the recruitment of the first 13 patients while data are being analysed for the first stage of inclusion.
- In order to account for not evaluable patients (+/- 10%), 47 patients will be recruited.

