#### **10.1.5. Phase II trial: Cohort A' (Colorectal @ 80 mg), with immune signature (based on low tumor-associated macrophages infiltrate level)**

- We rely on a single-arm phase 2 trial based on an optimal two-stage Simon's design [91].
- Treatment will be considered promising if 4-month PFR  $\geq 20\%$ .
- Hypotheses are the following:
  - 20% 4-month PFR (null hypothesis),
  - 40% acceptable 4-month PFR (alternative hypothesis),
  - 5% 1-sided type I error rate,
  - 80% power,
- A total of 43 eligible and assessable subjects will be necessary, with 13 assessable subjects recruited to the first stage.

- Stage 1: Following the inclusion of the first 13 assessable patients, if 3 or less patients are progression-free at 4 months (complete response, partial response or stable disease), the study will be terminated early. Otherwise, if 4 or more patients are progression-free at 4 months, the second group of subjects will be recruited.
- Stage 2: If at the end of recruitment, 13 patients or more are progression-free at 4 months (out of the 43 eligible and evaluable patients), treatment will be considered worthy of further testing in this disease (efficacy rate  $\geq 20\%$ ).
- Inclusions will not be suspended after the recruitment of the first 13 patients while data are being analysed for the first stage of inclusion.
- In order to account for not evaluable patients (+/- 10%), 47 patients will be recruited.

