#### **10.1.7. Phase II trials: Cohort K (HPV-associated cancer)**

- We rely on a single-arm phase 2 trial based on an exact single stage design (A'Hern).
- Treatment will be considered promising if 6-month DCR  $\geq 10\%$ .
- Hypotheses are the following:
  - 10% 6-month DCR (null hypothesis),
  - 25% 6-month DCR (alternative hypothesis),
  - 5% 1-sided type I error rate,
  - 80% power,
- A total of 40 eligible and assessable subjects will be necessary. If at the end of recruitment, 8 patients or more have disease control at 6 months (out of the 40 eligible and evaluable patients), treatment will be considered worthy of further testing in this disease (efficacy rate  $\geq 10\%$ ).
- In order to account for not evaluable patients (+/- 10%), 44 patients will be recruited.

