##### 10.3.2.2. PHASE II TRIALS

- All analyses will be descriptive; no p-values will be calculated.
- Analyses will be conducted independently for each phase II trial.
- Analysis of the primary efficacy endpoint will be analysed based on the eligible population assessable for efficacy (see chapter 10.2 for definition):
  - Each patient will be assigned one of the following categories:
    - Confirmed complete response (CR)
    - Unconfirmed complete response (CRu)
    - Confirmed Partial response (PR)
    - Unconfirmed Partial response (PRu)
    - Stable disease
    - Progression (Clinical PD and radiological PD will be reported separately)

- Inevaluable for response
- Depending on the cohort, the rate of objective response (ORR: CR, CRu, PR, PRu) under treatment or the progression-free rate (PFR: CR, CRu, PR, PRu, SD) will be reported:
  - All eligible and assessable patients (section 10.2) will be included in the denominator for the calculation of the ORR/PFR.
  - The 95% two-sided confidence limits will be provided for the ORR/PFR (binomial law).
  - First endpoint conclusions will be based on the ORR/PFR for all eligible and assessable patients (section 10.2) after centralized radiological review of the data.
- As regards to the other efficacy endpoints, the analyses will be carried out in the eligible and assessable population:
  - Each patient will be assigned one of the following categories:
    - Confirmed complete response (CR)
    - Unconfirmed complete response (CRu)
    - Confirmed Partial response (PR)
    - Unconfirmed Partial response (PRu)
    - Stable disease
    - Progression
    - Inevaluable for response
  - The rate of best overall response will be calculated as the number of patients alive with the best response (recorded from the start of the treatment) divided by the number of patients eligible and assessable (section 10.2).
  - The 6-month progression-free rate will be calculated as the number of patients remaining alive and progression-free at 6 months from the start of the treatment divided by the number of patients eligible and assessable (section 10.2).
  - The 6-month objective response rate will be calculated as the number of patients alive with complete or partial response at 6 months divided by the number of patients eligible and assessable (section 10.2).
  - The 95% two-sided confidence limits will be provided for the calculated rates (binomial law)
- The safety analysis will be performed on the safety population.

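### In cohorts H, I, A' and J–P the rate at which treatment is called promising is the null-hypothesis rate itself, which conflicts with the count rule that delivers the 5% one-sided error

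*Protocol*

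**What the plan says.** Sections 10.1.3 to 10.1.10 of the protocol cover ten cohorts: H, I and A' (Simon optimal two-stage) and J to P (A'Hern single-stage). All follow one template, shown here for cohort H in section 10.1.3:

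- A headline sentence: "Treatment will be considered promising if 6-month PFR" is at least 20%.
- The hypotheses: "20% 6-month PFR (null hypothesis"), against "40% acceptable 6-month PFR (alternative hypothesis"), with "5% 1-sided type I error rate" and 80% power.
- A stage 1 rule that stops the cohort "if 3 or less patients are progression-free at 6 months" among 13.
- A final rule that needs at least 13 of 43 progression-free patients, followed by a bracketed remark that the efficacy rate is 20% or more.

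The same headline appears for cohort A' in section 10.1.5 ("Treatment will be considered promising if 4-month PFR" is at least 20%) and for cohort K in section 10.1.7 ("Treatment will be considered promising if 6-month DCR" is at least 10%). In every one of these sections the headline figure and the bracketed figure equal the null rate.

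Section 9.2.1 defines 6-month PFR, 4-month PFR and 6-month DCR as proportions of patients. Section 10.3.2.2 bases the primary conclusion on the rate in eligible and assessable patients, calls all analyses descriptive, and adds: "The 95% two-sided confidence limits will be provided for the ORR/PFR (binomial law").

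**The concern.** The null rate is the rate that the design treats as not worth pursuing. A sentence that calls a result promising at that rate gives the reader two success thresholds in one section. Because section 9.2.1 makes PFR and DCR observed proportions, the plain reading of the headline is a cut-off on the observed result. A cohort that fails its test could then be reported as promising in the protocol's own words.

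The protocol treats the same number the opposite way elsewhere. For cohort B, also judged on 6-month PFR, section 10.1.2 sets 20% as the minimal threshold and recommends stopping for inefficacy when the rate is likely to be at or below it. In cohorts H, M and O, 20% on the same endpoint is labelled promising.

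**Working it through.** **Inputs** (sections 10.1.3 to 10.1.10). Stage 1 stops at 3 or fewer of 13 (H, A') or 2 or fewer of 13 (I). The null rate p0, alternative p1 and final boundaries are in the table.

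**Step 1: reproduce the count rules.** For a single stage, the probability of success at true rate p is P(X ≥ r), with X ~ Bin(n, p). For two stages it is the sum over x1 > r1 of P(X1 = x1) × P(X2 ≥ r − x1), with X1 ~ Bin(13, p) and X2 ~ Bin(n − 13, p). Setting p = p0 gives alpha and p = p1 gives power.

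| Cohorts | p0 / p1 | Boundary | Observed rate at boundary | Exact alpha | Exact power |
|---|---|---|---|---|---|
| H, A' | 20% / 40% | 13/43 | 30.2% | 0.0496 | 0.800 |
| I | 15% / 40% | 8/29 | 27.6% | 0.0500 | 0.907 |
| J, L, N | 15% / 35% | 8/28 | 28.6% | 0.0486 | 0.818 |
| K, P | 10% / 25% | 8/40 | 20.0% | 0.0419 | 0.818 |
| M, O | 20% / 40% | 12/35 | 34.3% | 0.0344 | 0.805 |

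Every rule meets its stated 5% one-sided error and its stated power (90% for I, 80% for the others). A search also returns the H, A' and I designs as the Simon optima, and the J–P sizes as the smallest that satisfy the A'Hern requirements.

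**Step 2: apply the promising sentence literally.** The smallest count with observed rate at least p0 is p0 × n, rounded up:

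- H, A': 0.20 × 43 = 8.6, so 9
- I: 0.15 × 29 = 4.35, so 5
- J, L, N: 0.15 × 28 = 4.2, so 5
- K, P: 0.10 × 40 = 4
- M, O: 0.20 × 35 = 7

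Counts from there up to one below the boundary are promising by the headline and fail the count rule.

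| Cohorts | Counts in conflict | P(rate ≥ p0) at p0 | Alpha of count rule | Difference |
|---|---|---|---|---|
| H, A' (stage 1 passed) | 9–12 of 43 | 0.204 | 0.050 | 0.154 |
| I (stage 1 passed) | 5–7 of 29 | 0.248 | 0.050 | 0.198 |
| J, L, N | 5–7 of 28 | 0.413 | 0.049 | 0.364 |
| K, P | 4–7 of 40 | 0.577 | 0.042 | 0.535 |
| M, O | 7–11 of 35 | 0.567 | 0.034 | 0.533 |

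The last column is the chance, when the true rate equals the null, that the two statements disagree. For H, A' and I the figures are joint with passing stage 1, which at p0 has probability 1 − 0.747 = 0.253 (H, A') and 1 − 0.692 = 0.308 (I). Without the stage 1 rule they would be 0.500 and 0.445.

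**Step 3: the planned interval.** Exact (Clopper-Pearson) 95% lower limits at the boundary counts are 17.2% (p0 20%), 12.7% (15%), 13.2% (15%), 9.05% (10%) and 19.1% (20%), all below p0. Wilson 95% limits exceed p0 for 8/28 (15.25%), 8/40 (10.50%) and 12/35 (20.83%), but not for 13/43 or 8/29. Exact 90% two-sided lower limits are 15.09%, 10.36% and 21.12% for the single-stage designs, above p0. For 13/43 they are 18.9% and for 8/29 14.5%, still below p0, because a fixed-sample interval ignores the stage 1 stopping rule.

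**The case against.** The strongest reply is that the counts are the only operational rules. They say when to stop and when to conclude, and they are right. The headline can be taken as introducing the hypotheses, and the bracketed remark, attached to the count, as the conclusion about the true rate. Nothing in the protocol says that 9/43 succeeds. On that view the 20–58% figures describe a rule that nobody intends to run, and for H, A' and I they combine the stage 1 rule of one criterion with the final threshold of another.

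Much of this stands. The figures are conditional and are not operating characteristics of the plan, and the charitable reading softens the bracketed remark. It does not rescue the headline. Section 9.2.1 makes PFR and DCR observed proportions, and section 10.3.2.2 ties the conclusion to the rate without mentioning the counts. Even as a statement about the true rate, at or above p0 includes the null itself, whereas rejecting the null supports only a rate above p0.

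A reader might also infer that the 95% interval contradicts the 5% one-sided design, since the exact interval covers the null at every minimum winning count. The protocol does not support that. The interval is descriptive and no rule requires its lower limit to clear p0. With 2.5% per side, an exact interval is expected to cover p0 at the boundary of a 5% one-sided test, and with Wilson limits this does not happen in J–P. Section 10.3.2.2 names only the binomial law, and the interval method, its level and any two-stage adjustment can be left to the statistical analysis plan. Making the exact 95% interval the criterion would do harm: in J–P it would require 9/28, 9/40 or 13/35 and cut power to about 69–70%.

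**Conclusion.** The point holds as a wrongly stated decision threshold in ten cohorts. The promising rate equals the null rate, while the count rule requires an observed 20.0% to 34.3%. A literal reading would put the false-positive rate at about 20% (H, A'), 25% (I), 41% (J, L, N), 58% (K, P) and 57% (M, O) instead of at most 5%. This assumes that the sentence is applied to the observed proportion, that the planned numbers of assessable patients are reached, and that stage 1 is respected in H, A' and I.

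It should not be read as an error in the designs: sample sizes, boundaries, alpha and power are all correct. Nor is the planned 95% interval an error.

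**What to change.** In sections 10.1.3 to 10.1.10, delete or replace the headline sentence and the bracketed efficacy-rate remark, so that the count is the sole success criterion:

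- H and A': at least 13/43 (30.2%), after at least 4/13 at stage 1
- I: at least 8/29 (27.6%), after at least 3/13 at stage 1
- J, L and N: at least 8/28 (28.6%)
- K and P: at least 8/40 (20.0%)
- M and O: at least 12/35 (34.3%)

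Word success as evidence that the true rate exceeds p0, and have section 10.3.2.2 refer to these counts for the primary conclusion. The cost is a text edit, with no new patients, data or recalculation.

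Optionally, report a two-sided 90% interval beside the descriptive 95% one, adjusted for the two-stage design in H, I and A', so that the interval shown matches the one-sided 5% test. This is a reporting preference and corrects no error.
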